
### Sample size

The sample size calculation was conducted with G*Power Version 3.1.9.2 and was based on the primary outcome analysis (difference in BMI, EDE total score and EDI total score between the baseline and 12-month follow-up assessment in the MANTRa intervention group). Based on previous studies, at least medium effect sizes (dz = 0.5) for the change in BMI and ED pathology can be expected [18, 67]. Using *t*-tests for paired samples, a sample size of 34 for the MANTRa group is needed to detect an effect size (dz) of 0.5 (alpha 5%) with a power of 80%. To account for a dropout rate of 25%, a total of 50 patients will be recruited for the MANTRa intervention group.

Furthermore, we plan to obtain the same number of patients (*N* = 50) for the control group. Sensitivity calculations revealed that differences in the primary outcome variables between the MANTRa and control group can be detected for small to medium effects (f = 0.14) (group x time interaction using general linear mixed models). Using multi-center recruitment, it is expected to reach the target sample size.

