### Statistical analysis

The primary statistical analysis will be based on the intention-to-treat principle, which means that participants will be analyzed in the group to which they were allocated irrespective of their compliance with the assigned treatment. Missing data will be imputed; the specific imputation model will be developed once the final data is available. *T*-tests for paired samples will be carried out for analyzing pre-post differences (T0-T2) in the three primary outcome variables (BMI, EDE, EDI-2). To account for multiple testing (three primary outcome variables) and the inflation of the Type I error rate, we will use Bonferroni correction to adjust the significance level (α = .017). Additionally, a completer analysis will be conducted as a secondary analysis. General linear mixed models will be used to measure effects between groups and over time (T0, T1, T2, T3) with using the treatment type (MANTRa vs. TAU) as between factor and assessment time (T0, T1, T2, T3) as within-factor. The treatment type x time interaction will indicate whether there is a difference in the course between the MANTRa and control group. Additional *t*-tests will be used to explore group differences between intervention (MANTR-a) and control group (TAU).

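### The sample size is calculated at a 5% level, but the three primary tests are judged at .017, so the stated 80% power is not delivered

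*Protocol article*

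**What the plan says.** The Sample size section of the protocol article ties its calculation to the primary analysis, which is the baseline to 12-month change in BMI, EDE and EDI within the MANTRa group. It expects that "at least medium effect sizes (dz = 0.5) for the change in BMI and ED pathology can be expected", and concludes that "34 for the MANTRa group is needed to detect an effect size (dz) of 0.5 (alpha 5%) with a power of 80"%. It then allows for loss: "To account for a dropout rate of 25%, a total of 50 patients will be recruited for the MANTRa intervention group".

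The Statistical analysis section plans paired t-tests for "pre-post differences (T0-T2) in the three primary outcome variables (BMI, EDE, EDI-2"). Because there are three primary outcomes, it adds that "we will use Bonferroni correction to adjust the significance level (α = .017").

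The Sample size section does not mention this adjustment. The Limitations section concedes low power only for small between-group effects, not for these within-group tests.

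**The concern.** Both sections describe the same tests: same arm, same three outcomes, same interval, same paired t-test. Only the significance level differs, and the level used for sizing is about three times the level used for the decision. The stricter threshold costs power, so 34 evaluable patients cannot give the stated 80%.

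This is the only power figure given for the primary tests. If it is too high, a non-significant primary outcome will be read as stronger evidence of no change than it is. The authors also intend to use the results to plan a larger randomised trial.

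**Working it through.** **Inputs from the protocol article**

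- Sample size section: dz = 0.5; alpha 5%; power 80%; n = 34; dropout 25%; 50 recruited to MANTRa.
- Statistical analysis section: three primary tests; level .017 per test (0.05/3 = 0.0167).
- Sidedness is not stated. Two-sided is inferred, because two-sided 5% gives 34 while one-sided 5% gives 27.

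**Formula**

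For a paired t-test with n complete pairs, the degrees of freedom are n − 1, the noncentrality is δ = dz·√n, and the critical value c is the 1 − α/2 quantile of t with n − 1 degrees of freedom. Power is the probability that a noncentral t variable with noncentrality δ exceeds c in absolute value. The lower tail is negligible here.

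**Step 1: reproduce the stated figure at α = .05**

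- n = 33: c = 2.037, δ = 0.5·√33 = 2.872, power 79.5%.
- n = 34: c = 2.035, δ = 0.5·√34 = 2.915, power 80.8%.

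The smallest n reaching 80% is 34, as stated. No multiplicity adjustment was built in.

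**Step 2: the same test at α = .017**

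| Complete pairs | c | δ | Power per outcome |
|---|---|---|---|
| 34 (stated requirement) | 2.514 | 2.915 | 65.6% |
| 37 | 2.503 | 3.041 | 70.3% |
| 38 | 2.500 | 3.082 | 71.8% |
| 44 | 2.483 | 3.317 | 79.4% |
| 45 | 2.481 | 3.354 | 80.5% |
| 50 (no dropout) | 2.471 | 3.536 | 85.2% |

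The requirement is 45 complete pairs. Using exactly 0.05/3 instead of .017 gives 65.3% at n = 34 and still requires 45.

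**Step 3: apply the protocol's own dropout**

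- Expected complete pairs: 50 × 0.75 = 37.5, so 37 to 38, with power of 70.3% to 71.8%.
- Recruits needed for 34 complete pairs: 34/0.75 = 45.3, so 46. Recruiting 50 leaves a margin of only 4.
- Recruits needed for 45 complete pairs: 45/0.75 = 60.
- With 50 recruited and complete pairs only, 80% power needs 45/50 = 90% retention, that is, dropout of at most 10%.

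**Step 4: effect detectable with 80% power at .017**

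- n = 34: dz = 0.58.
- n = 37 to 38: dz = 0.55 and 0.54.
- n = 50: dz = 0.47.

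**The case against.** The best reply is that the sentence names its own alpha and is correct at that alpha. The defect is a mismatch between two sections, not a slip in the calculation. That is fair, but the section says it is sizing the primary analysis, and the primary analysis uses .017.

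Other points reduce the size without removing the problem:

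- **Recruited number.** The 65.6% belongs to the stated requirement of 34. With 50 recruited and 25% dropout, the figure to compare with 80% is 70% to 72%. This stands: the practical shortfall is 8 to 10 points, not 14.
- **Imputation.** The primary analysis is intention-to-treat with imputed data, and eating disorder psychopathology is also measured at 6 and 18 months. Imputation may recover some information, so actual power could lie between about 70% (complete pairs only) and 85% (all 50 observed). The imputation model is not yet specified, and imputation does not in general restore everything lost. The 10% dropout limit is therefore a complete-case figure.
- **Larger effects.** The protocol treats 0.5 as a minimum. If the true dz were 0.55, power at .017 would be about 80% with 37 to 38 pairs; at 0.6, about 87%. But the 80% is claimed at 0.5.
- **At least one outcome.** Assuming dz = 0.5 on all three outcomes and equal correlations of 0 to 0.8 (not given in the protocol), simulation at n = 37 gives about 83% to 98% power for at least one significant result, and 36% to 56% for all three. The protocol states no such success criterion; its power is for a single test.
- **One-sided testing.** This does not help: n = 34 at one-sided .017 gives 75.7%, and 34 is not a one-sided figure.

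**Conclusion.** The concern holds. The calculation and the decision rule for the same three tests use different significance levels, and the stated 80% is not what the design delivers. At .017 and dz = 0.5, power per outcome is 65.6% with the stated 34 patients and 70% to 72% with the 37 to 38 expected after dropout; 80% needs 45.

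These figures assume two-sided tests, complete pairs and power counted per outcome. They do not depend on any outside value. Type I error control and the effect estimates are unaffected. The error lies in what the protocol says the trial can detect, and it needs correcting because it concerns the primary analysis.

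**What to change.** Rewrite the power statement in the Sample size section at the level the tests will use, for example:

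*At the Bonferroni-adjusted two-sided level of .017, 45 evaluable patients give 80% power for dz = 0.5. With 50 recruited and 25% dropout (about 37 evaluable), power per outcome is about 70%, and the effect detectable with 80% power is dz = 0.55.*

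Add that these figures are for complete pairs, before any gain from imputation. The cost is one paragraph and a less favourable power figure; recruitment need not change. Keeping 80% at dz = 0.5 with 25% dropout would instead mean recruiting 60.

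An optional alternative is Holm's procedure in place of plain Bonferroni. It controls the same error rate and is never less powerful. Under the assumptions used above for three outcomes at n = 37, simulated power per outcome is about 77% to 80%, against 70%. Power quoted for the first Holm step at .017 is thus a conservative figure. This option changes the primary testing rule after recruitment has started, so it needs a documented amendment before the data are analysed, as well as the rewording.

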## Materials and methods

### Study design

The trial described in this study protocol paper is a multi-center cohort study, which will evaluate the efficacy of MANTRa (*n* = 50) compared with TAU (*n* = 50) in a sample of adolescent and young adult outpatients with AN. Assessments will be conducted prior to intervention start (baseline, T0), at 6-month (T1), at 12-month (T2) and at 18-month follow-up (T3). Researchers who will not be involved in conducting the medical and psychotherapeutic ED treatment will assess the outcome variables.

Ethical approval was obtained from the Ethics Committee of the Medical University of Vienna (EK 2005/2017). The data collection in this study follows the ethical standards laid down in the 1964 Declaration of Helsinki and its later amendments. The trial was registered at clinicaltrials.gov (Identifier: NCT03535714).

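### The between-group sensitivity f = 0.14 is labelled small to medium, but on the G*Power interaction scale it is a difference in change of about 0.56 SD, which is medium by the protocol's own benchmark

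*Protocol article*

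**What the plan says.** The Sample size section names the software: "The sample size calculation was conducted with G*Power Version 3.1.9.2". The calculation that fixes the sample size is a paired t-test within the MANTRa group, sized to "detect an effect size (dz) of 0.5 (alpha 5%) with a power of 80" per cent. The section justifies that effect by saying that "at least medium effect sizes (dz = 0.5) for the change in BMI and ED pathology can be expected", so a standardised 0.5 is the protocol's own benchmark for medium. It then allows for attrition: "To account for a dropout rate of 25%, a total of 50 patients will be recruited for the MANTRa intervention group".

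For the comparison with TAU, with 50 patients in each group, the section gives only a sensitivity statement: differences "can be detected for small to medium effects (f = 0.14) (group x time interaction using general linear mixed models"). It states no alpha, power, within-person correlation, analysed N or number of time points for this figure, and does not translate it into SD or outcome units.

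The Statistical analysis section describes the between-group model with "assessment time (T0, T1, T2, T3) as within-factor", that is, four time points. Directly after the paired t-tests it says "we will use Bonferroni correction to adjust the significance level (α = .017"), and it does not say whether that level extends to the mixed model.

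**The concern.** The familiar benchmarks of 0.10 (small) and 0.25 (medium) belong to the ordinary between-group f, where two groups that differ by d have f = d/2. On that scale 0.14 lies between small and medium and corresponds to d = 0.28. The f of a repeated-measures interaction is built differently, and the same number stands for a larger difference between groups. Carrying the verbal label across makes the design look about twice as sensitive as it is.

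This matters because the Introduction hypothesises superiority over TAU on BMI and eating disorder psychopathology, and the treatment-by-time interaction is the test of it. A reader who believes that small-to-medium differences are detectable would take a non-significant interaction as evidence against such differences. The Limitations section also says the results may be used to design a larger randomised trial.

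**Working it through.** **Inputs.** From the protocol: f = 0.14; G*Power; 50 + 50 patients; 25% dropout (N = 75 by arithmetic, or 37 per group rounded down); four time points in the model; alpha 5% and 80% power (both stated for the paired test only); .017 (stated beside the paired tests). Assumed, because not stated: within-person correlation ρ = 0.5 (varied below), sphericity, and 80% power for the sensitivity run.

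**1. The paired-test figure.** dz = 0.5, two-sided 5%, n = 34 gives power 0.808. The protocol's 34 is reproduced.

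**2. The sensitivity figure.** In G*Power's default within-between interaction routine with two groups and m time points, the noncentrality is λ = f²·N·m/(1−ρ), with df₁ = m−1 and df₂ = (N−2)(m−1). For f = 0.14, N = 100, m = 2, ρ = 0.5, λ = 0.0196 × 200/0.5 = 7.84, and power at 5% is 0.79. Solving for 80% power gives f = 0.1415. The stated 0.14 is reproduced.

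The alternative SPSS-type scale would give 0.286 (m = 2) or 0.194 (m = 4) for the same design, so 0.14 fits the default scale.

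**3. Other inputs that also give about 0.14** (80% power):

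| Time points | N | ρ | alpha | f |
|---|---|---|---|---|
| 2 | 100 | 0.5 | .05 | 0.1415 |
| 4 | 75 | 0.5 | .05 | 0.136 |
| 4 | 100 | 0.3 | .05 | 0.139 |
| 4 | 75 | 0.6 | .017 | about 0.138 |

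Four time points with N = 100, ρ = 0.5 and 5% would give 0.118. The inputs actually used therefore cannot be recovered from the figure.

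**4. What 0.14 means in SD units.** With two groups and two times, a difference in change δ puts an interaction effect of ±δ/4 in every cell, so f = δ/(4σ). Hence δ = 4 × 0.14 σ = 0.56σ. Alpha, N and ρ do not enter this conversion.

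With four times, f is half the population SD, over time, of the group difference, divided by σ. The difference is therefore the pattern multiplied by 0.28/SD(pattern):

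| Group difference at T0, T1, T2, T3 (relative) | SD of pattern | Difference at 12 months |
|---|---|---|
| 0, 1/3, 2/3, 1 (linear to 18 months) | 0.373 | 0.50σ |
| 0, 0, 1, 1 | 0.500 | 0.56σ |
| 0, 1, 1, 1 | 0.433 | 0.65σ |
| 0, 0.5, 1, 1 | 0.415 | 0.68σ |
| 0, 0.5, 1, 0.5 (half fades by 18 months) | 0.354 | 0.79σ |

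**5. The same sensitivity as a two-sample t-test on T0–T2 change** (80% power, in SDs of the change score, the unit closest to the protocol's dz):

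| Per group | alpha | Detectable difference |
|---|---|---|
| 50 | .05 | 0.566 |
| 37 | .05 | 0.660 |
| 50 | .017 | 0.655 |
| 37 | .017 | 0.766 |

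At d = 0.28, 50 per group at 5% gives 28% power.

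**6. Dependence on correlation.** The SD of change is σ√(2(1−ρ)), which equals σ only at ρ = 0.5. In raw outcome SDs, the detectable difference for N = 100, two times and 5% is 0.67 at ρ = 0.3, 0.57 at ρ = 0.5 and 0.44 at ρ = 0.7.

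**The case against.** The strongest reply is that nothing has been miscalculated. That is true: 0.14 is reproduced, and it does lie between the usual small and medium cut-offs. But those cut-offs do not fit this scale, and the same section supplies a benchmark, 0.5 for medium, that the converted figure meets or exceeds.

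A reader might go further and infer that the figure ignores the Bonferroni level and the dropout. The documents do not support that. The inputs are unstated, and one set that includes both (four times, N = 75, ρ = 0.6, alpha .017) also gives about 0.14. The .017 level is placed with the paired tests and is not tied to the mixed model. Nor are the unstated inputs a fault in themselves, since a condensed article commonly leaves them to the full protocol.

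It is also fair to say that the stakes are limited. The sample size rests on the paired test, and the Limitations section admits that 50 per group may miss small between-group effects and that the comparison is observational. This softens the consequence but leaves the label uncorrected: a difference of 0.5 SD of change also falls short of 80% power with 50 per group at 5%, since 0.566 is needed.

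Finally, a high within-person correlation would make smaller raw differences detectable (0.44 SD at ρ = 0.7). That stands as a reason to state the correlation. It does not alter the meaning of f = 0.14.

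**Conclusion.** The point holds as a mislabelled sensitivity, not as an arithmetic error. On G*Power's default interaction scale, f = 0.14 is a between-group difference in change of 0.56 outcome SD with two time points. With four, it is about 0.50 to 0.68 SD at 12 months for most patterns and up to about 0.79 SD for a fading effect. This rests on the default scale having been used, which the reproduction supports, and on the time patterns shown.

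A reader might also conclude that the study can detect only medium-to-large effects. That needs the .017 level and the dropout loss to be added together (0.77 SD of change), and the protocol does not say that the first applies to this comparison. Severity is moderate to minor.

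**What to change.** Remove the small-to-medium label and express the sensitivity as a standardised difference in T0–T2 change with its assumptions. For example:

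*With 50 patients per group, two-sided alpha 5% and 80% power, the detectable difference in change is about 0.57 SD of the change score (a medium effect). With 25% dropout it is about 0.66. If the .017 level is also applied to this comparison, it is about 0.77.*

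Add that the value in raw outcome SDs depends on the within-person correlation (0.67, 0.57 and 0.44 at correlations of 0.3, 0.5 and 0.7 for N = 100, two times, 5%). If f = 0.14 is kept alongside, state the number of time points, correlation, N, alpha and power behind it. Also say whether .017 covers the between-group model.

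The cost is a sentence or two of text and a less favourable stated sensitivity. The sample size and the planned analyses do not change.

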### Data management

Self-rating questionnaires will be completed by the participants online via ‘Limesurvey’. Data from this survey tool will be directly imported into IBM Statistics SPSS software afterwards. Interview data will be entered manually by the research team. A data quality check will be carried out to exclude implausible values before the statistical analysis. Personal information allowing patients’ identification will be stored separately from study data in order to protect confidentiality. Only authorized persons of the MANTRa research team will have access to the trial data.

### Statistical analysis

The primary statistical analysis will be based on the intention-to-treat principle, which means that participants will be analyzed in the group to which they were allocated irrespective of their compliance with the assigned treatment. Missing data will be imputed; the specific imputation model will be developed once the final data is available. *T*-tests for paired samples will be carried out for analyzing pre-post differences (T0-T2) in the three primary outcome variables (BMI, EDE, EDI-2). To account for multiple testing (three primary outcome variables) and the inflation of the Type I error rate, we will use Bonferroni correction to adjust the significance level (α = .017). Additionally, a completer analysis will be conducted as a secondary analysis. General linear mixed models will be used to measure effects between groups and over time (T0, T1, T2, T3) with using the treatment type (MANTRa vs. TAU) as between factor and assessment time (T0, T1, T2, T3) as within-factor. The treatment type x time interaction will indicate whether there is a difference in the course between the MANTRa and control group. Additional *t*-tests will be used to explore group differences between intervention (MANTR-a) and control group (TAU).

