
However, it is unclear whether the high acceptability, low dropout rates or improvements in ED psychopathology observed in adult patients receiving MANTRA [18, 19] can be transferred to adolescents with AN. This paper is a study protocol for a multi-center cohort study assessing the feasibility, acceptability and efficacy of an adapted version of the MANTRA treatment program for adolescents and young adults with AN (subsequently named “MANTRa”) compared to psychotherapeutic treatment as usual (TAU). We hypothesize that patients in the MANTRa intervention group will show a BMI increase and a reduction of ED symptoms at 12 months compared to baseline and that MANTRa will be superior to TAU with regard to BMI increase, ED psychopathology and treatment acceptability.

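### Holm's procedure would give the three primary paired tests the same family-wise control as the fixed Bonferroni threshold with more power; the between-group tests of the same outcomes have no stated multiplicity rule

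*Protocol article*

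**What the plan says.** The Sample size section defines the primary outcome analysis as the change from baseline to 12 months within the MANTRa group on BMI, EDE and EDI. It expects that "at least medium effect sizes (dz = 0.5) for the change in BMI and ED pathology can be expected" and states that 34 MANTRa patients are "needed to detect an effect size (dz) of 0.5 (alpha 5%) with a power of 80" per cent. It continues: "To account for a dropout rate of 25%, a total of 50 patients will be recruited for the MANTRa intervention group".

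The Statistical analysis section names paired t-tests for T0–T2 on the three outcomes. It then says, with the number of primary outcome variables as the reason, "we will use Bonferroni correction to adjust the significance level (α = .017").

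The mixed models come after that sentence: "The treatment type x time interaction will indicate whether there is a difference in the course between the MANTRa and control group". Neither a significance level nor a multiplicity rule is given for them. The additional between-group t-tests are described as exploring group differences. The Introduction hypothesises that "MANTRa will be superior to TAU with regard to BMI increase, ED psychopathology and treatment acceptability". The Sample size section adds a sensitivity statement for the group comparison: "differences in the primary outcome variables between the MANTRa and control group can be detected for small to medium effects (f = 0.14"). It gives no alpha, power, number of time points or correlation for that figure.

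**The concern.** The article does not leave the multiplicity procedure open. It fixes single-step Bonferroni for the primary tests. Holm's procedure compares the smallest p-value with .05/3, the next with .05/2 and the largest with .05, and stops at the first failure. It rejects everything that Bonferroni at .05/3 rejects and sometimes more, with the same strong family-wise control under any dependence between the tests. Power matters here because the sample was sized at alpha 5% while the tests run at .017.

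Second, the same three outcomes are tested between groups under a stated superiority hypothesis. The reason given for correcting the paired tests, namely three outcomes, applies there too, but the correction sentence comes before those tests are introduced.

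**Working it through.** **Inputs.** From the Sample size section: dz = 0.5, alpha 5%, power 80%, dropout 25%, 50 recruited per group, f = 0.14. From the Statistical analysis section: three outcomes, .017. Assumed because not stated: two-sided tests, equal dz on all three outcomes, and correlations between change scores of 0 to .7.

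**1. The plan's own n.** A paired t-test has noncentrality dz·√n on n − 1 degrees of freedom. At two-sided .05 and n = 34, the noncentrality is 0.5·√34 = 2.92 and power is 0.808, so 34 reproduces. A one-sided test would give 27.

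**2. The same test at the corrected level.** At .05/3, 80% power needs 45 completers, or 45/0.75 = 60 recruited. With 50 recruited and 25% dropout, 37 or 38 complete (50 × 0.75 = 37.5). Power per test:

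| n | alpha .05 | .05/3 | .017 |
|---|---|---|---|
| 34 | 0.808 | 0.653 | 0.656 |
| 37 | 0.841 | 0.700 | 0.703 |
| 50 | 0.934 | 0.850 | 0.852 |

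**3. Holm against Bonferroni.** Three correlated paired tests were simulated, with 20,000 trials per setting and dz = 0.5 on all three. Entries are average power per outcome, that is, the expected number of rejections divided by 3.

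| n | correlation | Bonferroni .05/3 | Holm |
|---|---|---|---|
| 34 | 0 / .5 / .7 | 0.655 / 0.655 / 0.657 | 0.755 / 0.740 / 0.734 |
| 37 | 0 / .5 / .7 | 0.704 / 0.706 / 0.700 | 0.802 / 0.787 / 0.773 |
| 50 | 0 / .5 / .7 | 0.850 / 0.851 / 0.851 | 0.921 / 0.912 / 0.904 |

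At n = 37, correcting costs 0.841 − 0.700 = 14 points per test, and Holm returns 7 to 10 of them. At n = 50, the loss is 0.934 − 0.850 = 8 points, and Holm returns 5 to 7.

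**4. The rounding.** 3 × .017 = .051, and under independence 1 − (1 − .017)³ = .0501. Simulated family-wise error at .017 is .048, .045 and .041 at correlations .3, .5 and .7.

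**5. The between-group family, if each test were run at 5%.** Under independence, 1 − 0.95³ = 0.143. Simulation gives 0.135, 0.126 and 0.110 at correlations .3, .5 and .7.

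**6. Does f = 0.14 reveal the intended level?** Noncentral F with λ = f²·N·m/(1 − ρ), N = 100, ρ = .5 (assumed) and m time points:
- m = 2: detectable f at 80% power is 0.1415 at alpha .05 and 0.164 at .05/3.
- m = 4, the number of assessments in the planned model: detectable f is 0.118 at .05 and 0.134 at .05/3. Power at f = 0.14 is 0.844 even at .05/3.

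The figure is therefore compatible with either level, depending on inputs that the article does not state.

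**The case against.** Bonferroni is valid, prespecified and gives simple simultaneous confidence intervals, so preferring Holm could be called a matter of taste. The interval advantage is real. It does not alter the fact that, for the testing decision, Holm gives more power at the same error control.

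The figures at n = 37 may also be called pessimistic. The primary analysis is intention-to-treat with imputation, so the effective n lies between 37 and 50, and dz = 0.5 is stated as a minimum. That stands. It narrows the gain to about 5–7 points at n = 50 but does not remove it.

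On the between-group tests, a reader might infer that the plan runs them at an uncorrected 5%. The document does not say so. No level is stated, the f = 0.14 figure cannot settle it, and the correction is justified by the number of primary outcomes, so it can be read to cover both sets of tests. The level may also be set in an analysis plan that is not shown. Moreover, the Limitations section says that group differences are observational and not causal, and non-random assignment limits a superiority claim more than multiplicity does. This keeps the between-group point secondary, but the superiority hypothesis is still stated without a rule attached to its tests.

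**Conclusion.** The point holds for the choice of procedure. Under dz = 0.5 on all three outcomes and correlations of 0 to .7, Holm raises average power per outcome from about 0.70 to 0.77–0.80 at 37 completers and from 0.85 to 0.90–0.92 at n = 50. The gain depends on more than one outcome truly changing: if only one did, Holm would add little. Nor does it remove the mismatch between sizing at 5% and testing at .017; it recovers part of that loss.

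A reader might also infer that rounding .05/3 up to .017 loses power. It does the opposite, adding 0.2–0.3 points per test. Its only cost is a nominal bound of .051, which is trivial.

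For the between-group tests, the supported statement is that no level or multiplicity rule is given. The 11–14% family-wise error applies only if each is run at 5%.

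**What to change.** In the Statistical analysis section, replace Bonferroni at .017 by Holm's procedure on the three paired T0–T2 p-values, with ordered thresholds .05/3, .05/2 and .05, unrounded. Add that Holm is also applied, as a separate family, to the three treatment × time tests of BMI, EDE and EDI-2. The additional t-tests are already described as exploring group differences and need no change.

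This takes one or two sentences and no extra patients. There are two downsides. Simultaneous confidence intervals that match Holm's decisions are less simple than Bonferroni intervals. The between-group tests also face stricter thresholds if 5% was intended for each; with two time points and a correlation of .5, for example, the detectable f at the strictest step is 0.164 rather than about 0.14.
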